## Abstract

**Background:**

Surgery is a curative treatment for patients with locally advanced colon cancer, but recurrences are frequent for those with stage III disease. FOLFOX adjuvant chemotherapy has been shown to improve recurrence-free survival and overall survival by more than 20% and is nowadays considered a standard of care. However, the vast majority of patients will not benefit from receiving cytotoxic drugs because they have either already been cured by surgery or because their tumor cells are resistant to the chemotherapy, for which predictive factors are still not available.

Identifying which patients are unlikely to respond to adjuvant chemotherapy from among those who are eligible for such treatment would be a major step towards treatment personalization. It would spare such patients from unnecessary toxicities and would improve the allocation of societal healthcare resources.

**Methods/design:**

PePiTA is a prospective, multicenter, non-randomised trial built on the hypothesis that preoperative chemosensitivity testing using FDG-PET/CT before and after one course of FOLFOX can identify the patients who are unlikely to benefit from 6 months of adjuvant FOLFOX treatment for stage III colon cancer.

The study’s primary objective is to examine the ability of PET/CT-assessed tumor FDG uptake after one course of preoperative chemotherapy to predict the outcome of adjuvant therapy, as measured by 3-year disease-free survival.

Secondary objectives are to examine the predictive value of changes in PET/CT-assessed tumor FDG uptake on overall survival, to define the best cut-off value of FDG uptake for predicting treatment outcome, and to analyse the cost-effectiveness of such preoperative chemo-sensitivity testing.

At study planning, exploratory translational research objectives were 1) to assess the predictive value of circulating tumor cells for disease-free survival, 2) to examine the predictive value of single nucleotide polymorphisms for disease-free survival with respect to genes related either to toxicity or to drug targets, 3) to assess genomic rearrangements associated with response or resistance to FOLFOX treatment, 4) to identify an immunologic signature associated with metabolic tumor response to FOLFOX therapy and, finally, 5) to create a bank of frozen tumor samples for future studies.

**Discussion:**

PePiTA is the first study to use the primitive tumor chemosensitivity assessed by metabolic imaging as a guidance for adjuvant therapy in colon cancer. It could pave the way for tailoring the treatment and avoiding useless toxicities for the patients and inadequate expenses for the society. It could also give an interesting insight into tumoral heterogeneity, resistance to chemotherapy, genetic predisposants to oxaliplatin toxicity and immune response to cancer.

**EudraCT number:**

2009-011445-13

**Trial registration:**

ClinicalTrials.gov number, NCT00994864

## Background

### Adjuvant treatment of colon cancer

Colon cancer is a major public health problem accounting for over one million new cases per year worldwide [1]. Surgery is the only curative therapy available for localised colon cancer; however, the disease is associated with a significant recurrence rate for which the depth of tumor penetration within the intestinal wall and the presence of involved lymph nodes, as described in the TNM classification system [2], are major prognostic factors.

In stage III colon cancer, postoperative adjuvant chemotherapy is associated with a statistically significant improvement in disease-free survival (DFS) and overall survival (OS) compared to surgery alone. The National Surgical Adjuvant Breast and Bowel Project (NSABP) C-01 trial, reported in 1988, was the first study to show such a survival advantage [3]. Drug regimens were improved substantially over the years and a 6-month combination of 5 flurouracil (5FU), folinic acid, and oxaliplatin (FOLFOX) became the reference treatment in 2004 showing a 0.76 hazard ratio (HR) (95% confidence interval [CI] 0.62–0.92) for relapse favouring FOLFOX compared to fluorouracil plus folinic acid [4]. In a population of stage II-III colon cancer, FOLFOX is associated with a 3-year 72.2% DFS and a 78.5% 5-year survival rate. The current consensus is that adjuvant chemotherapy is indicated for stage III colon cancer. However, because of a lower magnitude of benefit, adjuvant chemotherapy remains controversial for stage II colon cancer, especially for low-risk patients [5].

Acute toxicity to the FOLFOX regimen in the adjuvant setting has been well described as moderate to severe [4], but very little is known with respect to long-term side effects. With delayed cardiac [6], cognitive [7,8] and oncogenic [9] side effects increasingly being reported in cancer survivors treated with adjuvant therapies, long-term side effects are a major concern associated with every treatment given with curative intent.

It is challenging to identify which patients are unlikely to benefit from adjuvant therapy, because no measurement is possible once a tumor has been removed. Being able to predict this successfully would bring great benefit, because this would potentially spare many patients from acute and delayed drug-induced toxicities, and avoid the useless spending of public and private healthcare resources.

Standard response measurements (WHO [10], RECIST [11], and modified RECIST [12]) rely entirely upon measuring the size of the tumor with computerized tomography scan (CT scan), ultrasound or magnetic resonance imaging (MRI) and only apply under restrictive conditions (well defined lesions, adequate minimum size, at least six weeks of chemotherapy). In the absence of any reliable chemosensitivity predictors, using such measurements to determine response means giving potentially ineffective treatments to patients for long periods of time.

However, early response detection techniques are now emerging, of which ^18^ F Fluorodeoxyglucose (FDG) positron emission tomography (PET)/CT and circulating tumor cells (CTCs) are the most promising.

### Positron emission tomography

The most frequently used tracer for PET/CT in the clinical setting is FDG, a marker of glycolysis, which is generally increased in malignant tumors. The uptake of FDG is related to the viable tumor cell load, and indirectly to the proliferative activity. PET/CT imaging has been able to measure a decrease in FDG uptake very early after exposure to treatment in various settings. In the context of neoadjuvant treatment of breast cancer, the reduction of FDG uptake measured at two weeks after the first dose of chemotherapy has been shown to predict the late FDG-PET/CT response measured four weeks after the end of chemotherapy, and to correlate with histopathological response [13].

A correlation between an early metabolic response after one or two courses of therapy and patient outcome has also been found in diffuse large cell lymphoma and Hodgkin’s disease [14], high-burden follicular lymphoma [15], lung cancer [16,17], and locally advanced oesophagogastric junction tumors treated with neoadjuvant chemotherapy [18]. In the latter indication, metabolic imaging-based assessment of response has already been used to develop trial designs aimed to tailor treatments according to the level of efficacy [19,20].

In advanced colorectal cancer, reports on the correlation of patient outcomes with FDG-PET/CT-based metabolic response assessment after 1 or 2 months of chemotherapy are inconsistent [21-23], probably partially because of methodological issues in multi-metastatic assessment. Early assessment after one course of therapy seems to be a more promising approach in light of recent findings that show excellent negative predictive value in the absence of morphological response and good correlation with the overall patient survival [24].

In locally advanced rectal cancer, several independent research groups have confirmed the high negative predictive value of metabolic assessment, demonstrating that the FDG uptake remains unchanged if the tumor is not sensitive to radio-chemotherapy [25,26].

### Circulating tumor cells

CTCs can be detected in the peripheral blood of patients with advanced tumors and could be useful to monitor treatment efficacy in metastatic colorectal carcinoma (CRC) [27-30] and breast cancer [31-33]. A recent report by Uen et al. suggests an association between the persistence of CTCs after curative surgery for CRC and recurrence risk [34]. No data exist concerning their use in the neoadjuvant setting to monitor therapeutic response. To assess the potential role of CTCs in locally advanced colon cancer, we designed a substudy in the PePiTA trial to analyze the prognostic value of baseline CTCs and the predictive value of CTC count modifications after one course of preoperative chemotherapy for adjuvant therapy outcome.

### Single nucleotide polymorphisms

Predicting the toxicity of anti-cancer drugs is complex. DNA changes (mutations, polymorphisms and gene hypermethylation) are increasingly implicated in the observed variation of toxicity among patients. Knowledge of these characteristics would allow treatments to be tailored according to individual susceptibility. This point will be addressed prospectively by performing single nucleotide polymorphism (SNP) testing before the preoperative course of chemotherapy.

### Genomic rearrangements

Recent advances in next generation sequencing (NGS) technologies and data analysis have enabled us to explore specific somatic rearrangements and aberrations in the cancer genomes of individual patients in a cost effective and time efficient manner [35]. Tumor cells releasing naked DNA into blood after apoptosis or necrosis provide hope for a new approach to cancer detection through the quantification and analysis of circulating free DNA. The idea of evaluating blood samples for mutant DNA is particularly attractive, not only because it could be used to detect several cancer types, but also because blood samples can easily be collected during patient follow-up as so-called “liquid biopsy” [36]. If the NGS analysis in this study demonstrates that the detection and quantification of specific tumoral genomic rearrangements in circulating DNA provides a sensitive and specific measure of disease progression, treatment response and prognosis in patients with colon cancer, this will have a major impact on the future clinical treatment of the disease.

### Tumor immune infiltration

At present, there are no clinical data available reporting the immune response (reflected by the type, density and function of tumor infiltrating lymphocytes (TILs)) of colon cancer after preoperative chemotherapy. Chemo- and targeted therapies that potentially stimulate the immune system [37] or inhibit Treg [38] could modify the immune infiltration of primary or metastatic tumors. In this regard, preclinical data (CRC cell lines) suggest that oxaliplatin induces immunogenic death of CRC cells, and that this effect determines its therapeutic efficacy in patients with CRC [39]. Therefore, in this study, particular attention will be given to the analysis of TILs in tumors resected after chemotherapy.

### Study hypothesis

PePiTA is built on the hypothesis that testing FDG-PET/CT metabolic changes before and after one course of FOLFOX given preoperatively will identify the patients with stage III colon cancer who are most unlikely to have significant benefit from adjuvant treatment using the same chemotherapy regimen after surgery for 6 months.

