## Methods

### Study design

PePiTA is a prospective, multicenter, non-randomised trial. Patients with histologically confirmed colon adenocarcinoma compatible with clinical stage III are eligible for study screening. The study design is illustrated in Figure 1.

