### Objectives

PePiTA’s primary objective is to examine the ability of PET/CT-assessed tumor FDG uptake after one course of preoperative chemotherapy to predict the outcome of adjuvant therapy, as measured by 3-year DFS among patients with pathological stage III.

Secondary objectives are to examine the predictive value of changes in PET/CT-assessed tumor FDG uptake on OS, to define the best cut-off value of FDG uptake for predicting treatment outcome, and to analyse the cost-effectiveness of such preoperative chemosensitivity testing.

Exploratory (translational research) objectives in the context of several sub-studies are 1) to assess the predictive value of CTCs for DFS, 2) to examine the predictive value of SNPs for DFS with respect to genes related to toxicity or drug targets, 3) to assess genomic rearrangements associated with response or resistance to FOLFOX treatment, 4) to identify an immunologic signature associated with metabolic tumor response to FOLFOX therapy and, finally, 5) to create a bank of frozen tumor and blood samples for future translational research studies.

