### Treatment

All eligible patients will undergo FDG-PET/CT imaging at baseline and then after one cycle of FOLFOX [3] preoperative chemotherapy (a 2-hour infusion of 200 mg/m2 leucovorin or equivalent, followed by a bolus of 400 mg/m2 fluorouracil and then a 22-hour infusion of 600 mg/m2 fluorouracil given on 2 consecutive days; a two-hour infusion of 85 mg/m2 oxaliplatin on day 0, simultaneously with leucovorin, using a Y-infusion device) followed by surgery.

After surgery, patients will be fully evaluable in the study and receive adjuvant FOLFOX when they meet the following criteria: the delay between the first PET/CT scan and the start of neoadjuvant FOLFOX was less than 7 days; the second PET/CT scan was performed on D14 (range: D13-D15); postoperative pathology confirms stage III (pTNM) adenocarcinoma of the colon; and CEA level measured one month after surgery is less than 1.5 × ULN.

All patients, both those meeting the inclusion criteria only and those fully evaluable for the primary objective, will be followed for DFS and OS assessment. Time zero for the assessment of time-to-event outcomes is the first day of pre-operative chemotherapy. In case a patient dies or is lost to follow-up before surgery, he or she will be excluded from the analysis of DFS and OS. The schedule of assessments is described in Figure 2.

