### FDG-PET/CT imaging

Whole body static FDG-PET/CT scans will be performed as described above. The local clinical investigators will be informed about the results of the baseline FDG-PET/CT. In case this scan shows suspicion of stage IV disease, a targeted confirmatory work-up is required before definite exclusion.

The results of the second FDG-PET/CT will be blinded to all local clinical investigators until there is formal documentation of relapse or progression.

Major efforts are undertaken to standardise patient preparation, FDG-PET/CT acquisition, image reconstruction, and semi-quantification of FDG uptake. This is centrally coordinated by the Imaging Core Lab at Institut Jules Bordet’s Nuclear Medicine Department. Strict standardisation will ultimately allow reliable pooling of the FDG-PET/CT imaging data from all participating centres. All participating FDG-PET/CT centres will be required to adhere to the quality assurance guidelines defined by the Belgian Hospital Physicists Association, and to perform a standard phantom (NEMA-type) acquisition, which will ultimately be used for a cross-calibration of all PET cameras.

The response assessment of the primary tumor will be performed according to the European Organisation for the Research and Treatment of Cancer (EORTC) guidelines: a metabolic response corresponds to a ≥15% decrease of the standardised uptake value max. In case of the presence of locoregional lymph node(s) observed on the baseline FDG-PET/CT, a similar response analysis will be performed for each lesion separately.

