### Follow-up

Follow-up procedures after completion of adjuvant treatment have to follow standard European clinical recommendations for patients with stage II and III colon cancer: every 3 months for the first 2 years and every 6 months for the next 3 years. This includes history and physical examination, serum CEA evaluation, chest X-ray (CT scan upon suspicion of lung metastases), and abdominal ultrasound or CT scan. Clinical follow-up data will be obtained for all patients, including those with stage II disease, with a minimum follow-up time of three years.

Stage IV diseases discovered at baseline FDG-PET/CT or during the surgical intervention deemed to remove the tumor, will not be followed afterwards within the study scheme.

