### Statistical considerations

Using data published by O' Connell and Laurie in patients with stage II-III colon cancer and a fixed-effects meta-analytic method, we determined a hazard ratio (HR) for DFS of 0.63 in favour of adjuvant 5-FU-based chemotherapy compared to follow-up only [48,49]. Because there is no evidence that the benefit of chemotherapy is different in stage II than in stage III colon cancer (Andre et al. did not identify any interaction between treatment and stage) [4], we hypothesised that this HR is applicable in a population of patients with stage III disease only. We further assumed that, for patients not responding to chemotherapy, the HR equals 1 (no benefit and no harm from chemotherapy).

We derived DFS at 3 years for stage III colon cancer from the MOSAIC trial (69%) [4]. From the previous assumptions, we expect DFS at 3 years to be 55% for non-responders and 83% for responders, in case of a 50% response rate. To detect this anticipated difference, if true, we need 33 events (α = 5% and β = 10%). To observe this number of events, we calculated that we needed 135 patients with pathological stage III disease and 225 patients to be registered in total, hypothesising that 60% of patients included in the trial will be documented with stage III colon cancer after surgery.

The trial will be regularly monitored to assess whether the observations are compatible with the expectations of 50% of eligible patients being assessed as PET responders after 1 course of FOLFOX and of 60% of screened patients with stage III. No data analysis about time-to-events variables will be conducted to make this adjustment.

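### The hypothesis and tailoring conclusion concern benefit from adjuvant FOLFOX, but the planned comparison can only show how PET response relates to DFS among patients who are all to receive it

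*Protocol article*

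**What the plan says.** - Study hypothesis: PET change before and after one course "will identify the patients with stage III colon cancer who are most unlikely to have significant benefit from adjuvant treatment" with the same regimen. The Abstract's Methods/design paragraph says the same in substance. The Discussion, in the Abstract and the main text, presents PET chemosensitivity as guidance for adjuvant therapy and, if the hypothesis is shown, as a route to tailoring it.
- Objectives: the primary objective is to examine the ability of PET-assessed uptake "to predict the outcome of adjuvant therapy, as measured by 3-year DFS among patients with pathological stage III".
- Study design: "PePiTA is a prospective, multicenter, non-randomised trial".
- Treatment: "After surgery, patients will be fully evaluable in the study and receive adjuvant FOLFOX when they meet the following criteria". The criteria are the timing of each of the two scans, pathological stage III, and a CEA limit after surgery.
- FDG-PET/CT imaging: "The results of the second FDG-PET/CT will be blinded to all local clinical investigators until there is formal documentation of relapse or progression". The scan therefore does not steer adjuvant treatment.
- Statistical considerations: "We further assumed that, for patients not responding to chemotherapy, the HR equals 1 (no benefit and no harm from chemotherapy"). From this and two borrowed figures (HR 0.63 for chemotherapy against follow-up only, and 69% 3-year DFS in stage III), the plan expects 55% in non-responders and 83% in responders. It requires 33 events, 135 stage III patients and 225 registered.
- Limitations in the Discussion: only the lack of a fresh pre-treatment biopsy, and its consequence for the genomic work, is named.

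**The concern.** Whether a group benefits from a treatment is a contrast between outcome with and without it. Everyone in the powered comparison is planned to have adjuvant FOLFOX, so the trial observes only one side of that contrast in each PET group. Worse DFS in non-responders could mean that FOLFOX does not work in them. It could also mean that their disease is more aggressive and FOLFOX works in them as well as in anyone else.

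The article has the ingredients of this distinction. Its Background names "the depth of tumor penetration within the intestinal wall and the presence of involved lymph nodes" as major prognostic factors, and its section on circulating tumour cells separates prognostic from predictive value. The Abstract notes that patients who do not benefit include those already cured by surgery. Such patients have good DFS, so DFS under treatment cannot tell them from patients whom chemotherapy saved.

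At stake is what a positive result may be said to show. The health economic analysis is also exposed, since it counts potential savings from identifying patients unlikely to respond.

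**Working it through.** **Inputs** (all from Statistical considerations): 3-year DFS in stage III 69%; chemotherapy HR 0.63; non-responder HR 1; response rate 50%; α = 5%, β = 10%. The sidedness of α is not stated.

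**Step 1. Reproduce the plan.**
- Untreated DFS implied by the inputs: 0.69^(1/0.63) = 0.555. With HR = 1 this is also the treated non-responder rate (stated as 55%).
- Responders: 2 × 0.69 − 0.555 = 0.825 (stated as 83%).
- HR, responders versus non-responders: ln(0.825)/ln(0.555) = 0.326. With the rounded rates: ln(0.83)/ln(0.55) = 0.312.
- Schoenfeld events, two-sided 5%, 90% power, equal groups: 4 × (1.960 + 1.282)² / (ln HR)² = 33.5 unrounded, or 30.9 with the rounded rates. The stated 33 is reproduced within rounding.
- Registration: 135/0.60 = 225, as stated.

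The sample-size arithmetic is sound.

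**Step 2. What the derivation assumes.** Overall untreated DFS is 55.5%. Non-responders are given 55.5% with or without treatment. With a 50:50 split, untreated responders must then be at 2 × 55.5% − 55.5% = 55.5%. So the plan also assumes, without saying so, that the PET groups have equal prognosis without chemotherapy. All of the 55% versus 83% gap is thereby attributed to treatment.

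**Step 3. A purely prognostic marker giving the same data.** Suppose FOLFOX has the same HR h in both groups. Untreated DFS is then (treated DFS)^(1/h):

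| Common HR h (assumed) | Untreated non-responders | Untreated responders | Gain, non-responders | Gain, responders |
|---|---|---|---|---|
| 0.50 | 30.3% | 68.9% | 24.8 points | 14.1 points |
| 0.63 | 38.7% | 74.4% | 16.3 points | 8.6 points |
| 0.76 | 45.5% | 78.3% | 9.5 points | 4.7 points |
| 1.00 | 55.0% | 83.0% | 0 | 0 |

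Every row gives treated DFS of 55% and 83%. At h = 0.63 the average untreated DFS is (38.7 + 74.4)/2 = 56.6%, close to the plan's implied 55.5%, so the scenario also fits the borrowed overall effect.

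**Step 4. Power.** The test sees only the treated groups. With 33 events its power is 89.5% (HR 0.326) or 91.8% (HR 0.312), whichever row is true. It cannot distinguish no benefit in non-responders from a gain of 16 or even 25 points.

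**The case against.** **The objective is within reach of the design.** A reader might infer that the trial cannot meet its primary objective. The text does not support that: the objective is to predict outcome under adjuvant therapy, and the design can do this. The mismatch lies in the hypothesis and the tailoring conclusion. This stands and limits the point.

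**The claim is softer than no benefit.** The hypothesis says benefit is most unlikely to be significant, and the Discussion is conditional. HR = 1 appears only as an openly labelled planning assumption. No rule for acting on a positive result is stated, so reading one into the article goes too far. Even the softer hypothesis, however, is about benefit.

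**The marker is a response to the same drugs.** PET change after FOLFOX is not an ordinary baseline feature, and equal efficacy in metabolic responders and non-responders may be less plausible than unequal efficacy. That is fair. Step 3 does not show the two explanations to be equally likely, only that the planned data cannot separate them.

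**Non-responders could be set against the historical untreated rate.** No such comparison is planned. With about 67 non-responders, ignoring censoring, the 95% CI around 55.5% is 0.555 ± 1.96 × √(0.555 × 0.445/67.5), or 44% to 67%. Taking the untreated rate as known, the HR runs from ln(0.673)/ln(0.555) = 0.67 to ln(0.436)/ln(0.555) = 1.41. Equal untreated prognosis would still be assumed.

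**Stage II patients might serve as untreated controls**, since "Clinical follow-up data will be obtained for all patients, including those with stage II disease". The article does not support this. All of them have one FOLFOX course, their later treatment is not stated, and stage differs by definition. Nor are they the only patients outside the evaluable set, because scan timing and CEA also exclude. There are at most 225 − 135 = 90 such patients. If 3-year DFS is 80% to 90% (an assumption), that means about 18 to 9 events. Against 33 stage III events, with events split equally by PET group, the SE of the interaction is √(4/33 + 4/18) = 0.59 to √(4/33 + 4/9) = 0.75. Power to separate HR 0.326 from HR 1 is then only about 48% to 32%.

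**An analysis plan may cover it.** Covariate adjustment and supportive analyses may well be there, and their absence here is no fault. No analysis supplies the missing comparator, though, and the hypothesis and design are fixed in this article.

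**Conclusion.** The point holds as a mismatch between claim and comparison. The trial can show whether PET response is associated with DFS under adjuvant FOLFOX. It cannot show that non-responders do not benefit, because that and equal untreated prognosis are assumed and never tested. With the plan's HR of 0.63 common to both groups, the same 55% versus 83% and the same power of about 90% coexist with a 16-point gain from chemotherapy in non-responders.

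The common HR is an illustration; the ambiguity holds for any common value. The argument takes adjuvant treatment as planned. Patients who happen not to receive it would not be a valid control.

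A reader might go further and call the study unsound or its sample size wrong. Neither follows: the event count reproduces, and a non-randomised marker study with a blinded second scan is a legitimate first step. This should be fixed, but it does not invalidate the data to be collected.

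**What to change.** 1. Restate the hypothesis and the intended conclusion, in the Abstract and the main text, as the association of PET response with DFS under adjuvant FOLFOX. The primary objective can stay as it is.
2. State that a positive result will not by itself be taken as evidence that non-responders do not benefit.
3. Add the missing untreated comparator to the limitations in the Discussion, and state the equal-prognosis assumption beside HR = 1 in Statistical considerations.
4. Present the cost-effectiveness results over a range of assumed non-responder HRs, not HR = 1 only. The article does not describe the economic model, so this may need only confirmation.
5. As supportive analyses, report the stage III HR adjusted for pT, pN and baseline SUVmax, which pathological staging and the baseline scan already provide. The stage II association may be reported descriptively, with any adjuvant therapy recorded. Neither analysis settles prognostic versus predictive.

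Cost: wording, a sensitivity range in the economic analysis and supportive analyses on data largely collected already; a record of adjuvant therapy in stage II may need adding. No change to sample size or patient schedule is needed. The downside is a more modest claim.
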